**6.2 Description of the treatment**

**6.2.1** **Control Area (Standard of Care)**

Patients with hypertrophic scarring usually undergo massage therapy, pressure garment application and/or steroid or fluorouracil injection as part of standard practice. At present, alternative treatments include cryotherapy, microneedling, fat transfer and Laser Therapy.

As these patients have various laser therapy to different parts of the body over a period of months or years, the control scar, if deemed of inferior quality to the laser treated area, will be treated as part of the patient routine ongoing management of their scars after the trial is completed.

**6.2.2** **Treatment Area**

Participants will undergo Ablative CO2 Laser treatment as part of standard of care. Typically, the laser treatment will be performed under local anaesthetic and will be conducted by a suitably trained medically qualified doctor, as the patients have agreed to participate in the research study, the doctor will also require knowledge of the research protocol.

The treatment will use a Lumenis® UltraPulse® CO2 laser device with the DeepFX^TM^ and/or SCAARFX^TM^ headpiece depending on scar thickness assessed by ultrasound prior to treatment. The proposed treatment area will be marked and photo documented. The treatment will include a single pass of the chosen treatment site with the following settings: SCAARFX^TM^: Energy 110-150 mJ; Density 3%; Shape: setting 2; Size: setting 10; Pulses 1; and DeepFX^TM:^ Energy 17.5-20.0 mJ; Density 5%; Shape: setting 2; Size: setting 10; Pulses 1. Repeat rate rate 0.5 -1 seconds; Frequency 250-300Hz; No active cooling will be used during the treatment.

Laser treatment during the trial will only be carried out on the randomised scar. No additional laser treatment will be done on other areas outside the randomised scars throughout the study period.

**6.3 Concomitant therapy**

Control and laser treated (randomised) scars, when healed, will be treated as per Standard of Care which would include silicone, massage and pressure therapy, when applicable.

1. **STUDY ASSESSMENTS**
   1. **Safety Assessments**

**7.1.1 Risk**

The risks associated with this study are related mainly to the potential adverse effects of CO2 laser therapy. In general, the clinical consensus regarding CO2 laser treatment of hypertrophic scars is that this therapy is well tolerated, and that adverse events related to treatment are rare. Nevertheless, we intend to rigorously and prospectively monitor, record and report adverse events to protect subject safety and evaluate prospectively the aforementioned current clinical consensus

Furthermore, all subjects may experience pain at the treatment site which is is expected to resolve within 3 days. Weeping and later crusting, itch, as well as treatment-related transient skin color changes are all expected to resolve up to 6 months after each treatment.

Specific treatment-related events that each site will be instructed to look for include:

- cellulitis
- superficial thrombophlebitis
- epidermolysis
- bullous conversion of treatment site
- herpetic vesicles or shingles lesions
- hypopigmentation
- hyperpigmentation
- severe or prolonged pain
- severe or prolonged itch

Severe events, such as necrotizing soft tissue infection, as well as full-thickness dermal injury (which could require skin grafting) are anticipated to be rare.

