**7.2.2 Adverse Event Recording and Reporting**

As this is an observational cohort study examining the effect of laser treatment which is administered as part of standard of care, pursuant to SOP for REC version 7.4, only serious adverse events (SAEs) where in the opinion of the Chief Investigator (CI) are related to the study (i.e., resulted from administration of any research procedures such a tissue biopsies or blood sampling) and unexpected (i.e., not listed in the protocol as an expected occurrence) should be reported to REC. Report of related and unexpected SAEs should be submitted to REC within 15 days upon CI’s knowledge of the event using the SAE form for non-CTIMPs published on the HRA website.

All AEs and SAEs will be recorded and reported on throughout the duration of the study. The Investigator will then record all relevant information in the CRF/SAE log.

Information to be collected includes:

- Type and details of event
- Event duration
- Investigator assessment of severity and causality and if the event was expected or unexpected
- Action taken
- Date of resolution
- Treatment required, investigations needed and outcome.

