**7.5 Schedule of Assessments and Data Collection**

**7.5.1 Baseline Data Collection (Recruitment/pre-assessment)**

Before any study related data or specimens are taken, the researcher will ensure that informed consent has been obtained and confirm that the trial subject meets the inclusion and non of the exclusion criteria. The study personnel will then collect and record the following information in the paper CRF booklet and eCRF (electronic case report form):

- Baseline patient information (age, sex, ethnicity, comorbidities, pre-injury medications)
- Burn/ trauma mechanism e.g. flame, scald etc.
- Anatomical location of scar to be treated with Laser therapy (wound map)
- Medical co-morbidities including Psychiatric or Behavioural Problems
- Subjective scar questionnaires - VSS, POSAS, BBSIP, QoL questionnaire (EQ-5D)
- Objective scar assessments – 3D camera, DSMII Colorimeter®, Dermascan® & Cutometer®.
- Clinical photograph of area of interest (treatment and control)
- Blood sample
- 2 Punch Biopsies (5mm) of scar tissue from identified sites that will be randomised for control and treatment area
- Punch Biopsy (5mm) of comparable normal skin.

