## Statistical Analysis

The primary comparison groups will be the scar sections randomised to (control group) versus those randomised to treatment with laser therapy (experimental group). Outcome data will be collected at pre-laser, 3 weeks post the first and third treatments and 12 month

s post third treatment.

All analysis will be based on the intention to treat principle, i.e. all scars will be analysed in the treatment group to which they were randomised irrespective of compliance with the allocated treatment or other protocol deviation. The data analysis for this pilot trial will be descriptive and mainly focus on confidence interval estimation, with no formal hypothesis testing performed.

Dichotomous feasibility measures, like the recruitment and retention rates, including completeness of data will be reported as numbers and percentages. These values will be summarised across participants or treatment groups as appropriate.

Given this study is a pilot, the data will help inform the selection of the most appropriate primary outcome measure for a larger RCT and provide data to estimate the sample size required for the main RCT.

Analysis methods will be chosen according to the data type; 1. Continuous endpoints (e.g. VSS total score): These data will be summarised using means and standard deviations, with differences in means with 95% confidence intervals reported. Longitudinal plots of the data over time will also be constructed for visual presentation of the data. 2. Categorical (dichotomous) endpoints (e.g. rates of improvement in scar domains): The number and percentages of participants/scars experiencing the event will be summarised across and between groups.

As this is a randomised study, there are no priori subgroup analyses specified.

Every attempt will be made to collect full follow-up data on all study participants with the anticipation that missing data will be minimal. The assessment of missing data is an outcome measure of this study.

If a suitable primary outcome is identified during the pilot trial, the level of missing data will form one component of the assessment of feasibility for a future trial. As this is a pilot trial, no formal sensitivity analysis will be conducted.

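### Laser harms are sought as treatment-related events, with no stated equal search of the control scar and no item for the affected scar, so local events cannot be reliably compared between scars

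*Protocol*

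**What the plan says.** **Aim.** Section 7.1.1 describes a clinical consensus that CO2 laser treatment is well tolerated and that treatment-related adverse events are rare. It says the study will monitor events in order to "evaluate prospectively the aforementioned current clinical consensus".

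**Search.** The list in 7.1.1 opens with "Specific treatment-related events that each site will be instructed to look for include" and names cellulitis, superficial thrombophlebitis, epidermolysis, bullous conversion, herpetic or shingles lesions, hypopigmentation, hyperpigmentation, severe or prolonged pain, and severe or prolonged itch. One entry is tied by its wording to the lasered area: "bullous conversion of treatment site". The paragraph on expected effects says that "all subjects may experience pain at the treatment site".

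**Recording.** Section 7.2.2 says "All AEs and SAEs will be recorded and reported on throughout the duration of the study". The items to collect include type and details, duration, action taken, resolution and outcome, and "Investigator assessment of severity and causality and if the event was expected or unexpected". None names the scar concerned. In Appendix A, footnote 4 (treatment site) records only the location of the scar to be lasered.

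**What both scars have in common.** Each receives a baseline punch: "2 Punch Biopsies (5mm) of scar tissue from identified sites that will be randomised for control and treatment area". Under section 6.1, both scars are assessed before randomisation and before each laser treatment. Appendix A repeats the scales at final follow-up and photographs both areas at those visits and at Day 22.

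**Analysis.** Section 8.2 makes the randomised scars the primary comparison groups. For dichotomous endpoints it says: "The number and percentages of participants/scars experiencing the event will be summarised across and between groups". The example given there is improvement in scar domains, not adverse events.

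**The concern.** The design supplies a concurrent control within each patient: a comparable scar, allocated at random, seen at the same visits and punched at baseline. The plan for harms does not use it. Labelling the listed events as treatment-related presumes the answer that the control scar could help to give.

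Most of the listed events can arise without laser. A local infection can follow a punch wound that is left unsutured (7.3.3.1), and both scars have one. Participants must have symptomatic hypertrophic scars (4.3), so itch, pain or altered pigment may be present before treatment.

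If the lasered scar is searched with a checklist and the control scar is not, a difference in counts partly reflects the search. If only the lasered scar is counted, the total mixes laser effects with biopsy effects and the natural course of the scar. Separating them then depends on the investigator's opinion. Section 5.4.3 masks the scar assessor and the data analysts; it does not mention the investigator who judges causality.

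**Working it through.** The plan states no figure on this point, so the check sets the sections side by side and counts.

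**1. Which listed events have another measure on both scars?**

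- A related scale measure exists for 4 of 9: hypopigmentation and hyperpigmentation (VSS pigmentation item, colorimeter), pain and itch (POSAS patient items).
- None exists for 9 − 4 = 5: cellulitis, thrombophlebitis, epidermolysis, bullous conversion, herpetic or shingles lesions. These depend on adverse-event recording and photographs.

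**2. When are those measures taken?** Appendix A places the scales and colorimeter at baseline, Month 3, Month 6 and final follow-up. At Day 22, the first visit after the day of laser treatment, there are adverse events and photographs but no scales. At that visit all nine events depend on the adverse-event record and photographs.

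**3. How comparable are the scars at each visit?** Punches are counted from 7.5.1, 7.5.3, 7.5.5, 7.5.6 and Appendix A, before any punch or laser treatment due at that visit:

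| Visit | Laser treatments so far (lasered scar) | Punches so far, lasered scar | Punches so far, control scar |
| --- | --- | --- | --- |
| Day 22 | 1 | 1 | 1 |
| Month 3 | 1 | 2 | 1 |
| Month 6 | 2 | 2 | 1 |
| Final follow-up | 3 | 3 | 1 |
| Whole study, including final punches | 3 | 4 | 2 |

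Up to the Day 22 punch the scars differ by laser treatment and not by number of biopsies. After it, the lasered scar carries one extra punch, then two (4 − 2 = 2 over the study). Later differences therefore combine laser with the additional biopsies.

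**4. What precision would a by-scar comparison have?** The protocol gives no event rates, so this step rests on assumptions. Let b be the proportion of patients with the event on the lasered scar only, c the proportion with it on the control scar only, and d = b − c. The Wald 95% interval is d ± 1.96 × √((b + c − d²)/n). With 20% drop-out, n = 60 × 0.80 = 48 pairs.

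| Assumed b / c | d | 95% CI |
| --- | --- | --- |
| 10% / 2% | 8% | −1.5% to 17.5% |
| 20% / 5% | 15% | 1.5% to 28.5% |
| 30% / 10% | 20% | 3.0% to 37.0% |

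First row: √((0.12 − 0.0064)/48) = 0.0486, and 1.96 × 0.0486 = 0.095. The table shows only what precision to expect; the point does not rest on it.

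**The case against.** The strongest reply is that nothing confines the search to one scar. In the list's introduction, 'each site' most naturally means each hospital, and only one of the nine entries is tied by wording to the lasered area. Section 7.2.2 covers all adverse events, its list is open-ended, and its type-and-details item can hold a location. The CRF is not shown. **This stands.** A reader might infer that the control scar is excluded from the search, or that events are not recorded by scar at all. The text supports neither. It supports only that equal search and location are not specified.

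A reader might also infer that control-scar events are lost unless the patient volunteers them, or that the trial can say nothing about attribution. Neither follows. Both scars are photographed at every visit after Day 1, and four of the nine events have a related measure on both scars. Two of those four are listed only when severe or prolonged, so ordinary scar symptoms would not qualify.

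Nor does 8.2 require adverse events to be counted by scar. Its rule concerns endpoints, adverse events are not among those in 2.2, and a participant-level count would satisfy its wording.

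Finally, this is a descriptive pilot, and under the assumed rates above the paired intervals are wide. That limits what can be concluded; it does not justify searching the scars unequally. The format of a safety table can be left to the SAP. Which scar is searched and what is recorded are data-collection rules, and an SAP cannot recover what was not collected.

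**Conclusion.** The point holds as a gap between the aim in 7.1.1 and the means specified for it. Active search is framed around treatment-related events, an equal search of the control scar is not stated, and the affected scar is not a specified data item. Local adverse events therefore cannot be reliably compared between the randomised scars, and attribution falls to investigator opinion.

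The extent is five of nine listed events throughout and all nine at Day 22. For pain, itch and pigmentation at the other assessment visits the gap is much smaller. No numerical bias can be given, because the protocol has no adverse-event rates.

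This is a cheap improvement and does not undermine the pilot's other aims. It assumes that the CRF adds no location item or two-scar checklist; if it does, the protocol need only say so. Equal search would not mask whoever completes the checklist, and location coding would not separate laser from the extra biopsies after Day 22.

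**What to change.** - **7.1.1:** call the nine entries 'local' events instead of treatment-related ones. Complete the list for both randomised scars at baseline, before the first laser treatment, and at each visit that already collects adverse events (Day 1, Day 22, Month 3, Month 6, final follow-up). At Day 22, complete it before the punch. The baseline round keeps existing itch, pain and pigment change from being counted as new.
- **7.2.2:** add a required location item with four values: laser scar, control scar, normal-skin biopsy site, elsewhere or systemic. Keep the causality assessment alongside it.
- **8.2:** report each local event by scar, with the within-patient difference in proportions (laser minus control) and a paired 95% confidence interval. Give the comparison up to the Day 22 punch separately, and state that later comparisons combine laser with the lasered scar's extra biopsies (four against two). This stays descriptive, in keeping with the pilot.

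**Cost:** one CRF item, a checklist for two scars at 1 + 5 = 6 existing visits, and one more table. No visit or procedure is added. The downside is a few minutes per visit and more minor control-scar events on record.

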**7.2 Safety Reporting**

**7.2.1 Serious Adverse Events**

Clinical, research team and the trial investigators will closely monitor safety of all trial subjects throughout the duration of the study. In the event that any adverse events occur they will be recorded and reported immediately according to the Standard Operating Procedures (SOP) for Research Ethics Committee (REC) version 7.4. This SOP provides the definition of a SAE. Any possible serious events that could possibly be study related will be reviewed and reported electronically within 24 hours by the study PI to the study sponsor (R&D Department, UHBFT).

**7.2.2 Adverse Event Recording and Reporting**

As this is an observational cohort study examining the effect of laser treatment which is administered as part of standard of care, pursuant to SOP for REC version 7.4, only serious adverse events (SAEs) where in the opinion of the Chief Investigator (CI) are related to the study (i.e., resulted from administration of any research procedures such a tissue biopsies or blood sampling) and unexpected (i.e., not listed in the protocol as an expected occurrence) should be reported to REC. Report of related and unexpected SAEs should be submitted to REC within 15 days upon CI’s knowledge of the event using the SAE form for non-CTIMPs published on the HRA website.

All AEs and SAEs will be recorded and reported on throughout the duration of the study. The Investigator will then record all relevant information in the CRF/SAE log.

Information to be collected includes:

- Type and details of event
- Event duration
- Investigator assessment of severity and causality and if the event was expected or unexpected
- Action taken
- Date of resolution
- Treatment required, investigations needed and outcome.

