# STUDY DESIGN

**3.1** **Methodology**

This is a multicentre intra-patient randomised controlled longitudinal observational cohort study, with parallel assignment, single blinded clinical trial to test the effect of ablative fractionated CO_2_ laser on hypertrophic scarring. Two anatomically comparable and independent scars would be selected per subject and randomly allocated to receive either fractioned CO_2_ laser therapy or standard care. An independent assessor will be blinded to the intervention and the control scars sites.

The study will collect quantitative data through tissue and blood samples to assess the cellular and molecular biomarkers response to laser therapy and qualitative data using a series of patient reported outcome measures (PROMs) and scar assessments. Scars will be subjectively assessed using the standard of care scar assessments; Modified Vancouver Scar Scale (mVSS), Patient and Observer Scar Assessment Scale (POSAS)*,* Brisbane Burn Scar Impact Profile (BBSIP). Scars will also be objectively assessed using 3D Vectra Photography for scar site identification, high resolution ultrasound for thickness, Cutometer^®^ for elasticity and colour using DSMII Colorimeter® camera.

As part of the evaluation of the impact of laser treatment on patients’ quality of life a PROMS validation study will be carried out to evaluate if the BBSIP is a useful tool for evaluating the impact of laser therapy on scar tissue and quality of life.

PROMs describe how the patient is functioning or feeling without input from clinical staff (17) providing a unique perspective of patients’ lived experience of the disease as not all symptoms or impacts are obvious to clinicians (18). In order for PROMs to be effective in clinical trials and practice, they have to capture information on domains that matter to the patient (17).

A previous study carried out in Birmingham (13) identified that there were a number of important domains for patients with burn injuries and these were applicable when evaluating relevant interventions. These include: scarring, movement and function, scar sensation, psychological distress, body image and confidence, engagement in activities, treatment burden and impact on relationships.

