## Randomisation

**5.4.1 Randomisation Procedures**

Each patient will have their own control scar in an anatomically comparable site either on the trunk or limbs. Allocation of scar treatment will be performed using randomisation. Two comparable anatomically scarred areas > 25 cm^2^ on trunk, arms or legs will be identified on the same patient and will be described as location A and location B on the body map. The patient’s identified scar site, A and B, will be randomised on a 1:1 basis to either the standard of care or laser treatment as shown in Table 1.

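### Section 7.2.2 defines relatedness by research procedures only, so an unexpected serious injury from the randomised laser would not trigger the 15-day ethics committee report

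*Protocol*

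**What the plan says.** Section 7.2.2 sets the rule for reporting to the REC. It opens with its reason: "As this is an observational cohort study examining the effect of laser treatment which is administered as part of standard of care". It then restricts reporting to serious adverse events that the Chief Investigator considers related to the study, glossed as "resulted from administration of any research procedures such a tissue biopsies or blood sampling", and that are also "unexpected (i.e., not listed in the protocol as an expected occurrence) should be reported to REC". Events meeting both conditions "should be submitted to REC within 15 days".

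Section 7.2.1 sets a separate route to the sponsor: "Any possible serious events that could possibly be study related will be reviewed and reported electronically within 24 hours by the study PI". It does not define study-related. Section 7.2.2 also requires every adverse event, serious or not, to be recorded with severity, causality, expectedness and outcome.

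On risk, section 7.1.1 says: "The risks associated with this study are related mainly to the potential adverse effects of CO2 laser therapy". On design, section 5.4.1 says that each participant's two scar sites "will be randomised on a 1:1 basis to either the standard of care or laser treatment". Section 3.1 combines both descriptions in one phrase: "intra-patient randomised controlled longitudinal observational cohort study".

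**The concern.** The definition of relatedness rests on a description of the study that the protocol contradicts elsewhere. If the laser were ordinary care that the study merely observed, confining relatedness to biopsies and blood samples would be coherent. But the protocol decides by randomisation which scar is lasered, and fixes when and at what settings. Harm from those sessions is then a consequence of taking part.

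What is at stake is timely external oversight of the risk that the protocol itself puts first. An independent committee would hear within 15 days of an unexpected serious biopsy complication, but not, under the literal rule, of an unexpected serious laser injury. Section 8.4 does not fill the gap: its three-monthly analysis concerns data quality and whether some blood tests can be dropped, and it describes no safety review.

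**Working it through.** No power, alpha or event-count formula applies, and the protocol states no figure to reproduce. The check has three parts.

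**1. Is the laser usual care or the study intervention?**

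| Protocol section | How it treats the laser |
| --- | --- |
| 7.2.2 | Usual care in an observational cohort |
| 6.2.2, opening | Given as part of usual care |
| 6.2.1 | One of several current alternative treatments; patients described as having laser to various body areas over time |
| 5.4.1 and Table 1 (5.4.2) | The randomised alternative to standard care |
| 8.2 | The experimental group, compared with control |
| 6.1 | Three sessions at set times; laser to the control scar only after study completion |
| 6.2.2, remainder | Device and settings specified; no laser outside the randomised scar during the study |
| 6.3 | Standard care described as silicone, massage and pressure therapy |
| 7.2.3 | A pregnant participant stops laser but goes on receiving standard care |

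The first three rows support the premise of 7.2.2. The other six treat the laser as something the trial allocates and controls, distinct from the standard-care comparator. The pregnancy rule makes sense only if laser is not itself the standard care meant there.

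**2. What happens to an unexpected serious laser injury under the rules as written?**

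- Recording (7.2.2): yes. All adverse events are recorded, and Appendix A schedules their collection at every visit from Day 1.
- REC report within 15 days (7.2.2): not triggered. The gloss on relatedness begins with *i.e.*, so it reads as a definition. The examples are open-ended, but the same sentence gives the laser's usual-care status as the reason for the restriction, so the laser cannot readily be read into the list.
- Sponsor report within 24 hours (7.2.1): uncertain. The threshold of possible relation to the study is broad enough to include the laser, but the only gloss on relatedness in the protocol is the narrow one in 7.2.2.
- The sentence in 7.2.1 on immediate reporting does not settle the matter, because it defers to the same REC procedure that 7.2.2 invokes for its restriction.

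**3. How much exposure is concerned?**

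- Inputs: 3 laser sessions per participant (6.1) and 60 participants (4.1).
- Ceiling: 3 x 60 = 180 sessions.
- Section 8.1.1 allows for 20% drop-out. If 20% of the 60 dropped out, 60 x 0.80 = 48 would complete, giving 3 x 48 = 144 sessions plus any that the other 12 received before leaving. The total would then lie between 144 and 180.
- This counts sessions, not events. The protocol gives no rate of serious events, so the number of reports affected cannot be calculated.

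**The case against.** The usual-care description is not peculiar to 7.2.2: sections 6.2.1 and 6.2.2 also use it, and section 6.1 aligns the visits with usual care. The rule is said to follow a named REC procedure, version 7.4, which is not available here, so what that procedure itself means by related cannot be checked. The list of research procedures is illustrative. These points stand to this extent: the request should be to reconcile the passages, not simply to delete one rationale. They do not remove the conflict, because the protocol's own text adopts a definition that its randomised design contradicts.

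A reader might draw three stronger conclusions that the text does not support.

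- *That serious laser harm escapes all expedited reporting.* The 24-hour sponsor route is in a different section and has a different recipient, decision-maker and threshold. It follows soon after the statement that the study's risks come mainly from the laser. It may well catch such events; it is only not secured.
- *That a severe laser injury is excluded twice, because naming it in 7.1.1 makes it expected.* The test in 7.2.2 is whether an event is listed as an expected occurrence, not whether it is mentioned. Section 7.1.1 sets necrotizing infection and full-thickness injury apart as severe and rare, and never calls them expected. Their status is unclear, not settled.
- *That the pilot's safety data would be incomplete.* All adverse events are recorded, and sites are told which laser events to look for. Who receives an expedited report does not change the dataset.

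**Conclusion.** The point holds for one route. As written, section 7.2.2 leaves an unexpected serious injury from the allocated laser outside the 15-day REC report, although the laser is the randomised experimental treatment and the main risk that the protocol names. The 24-hour sponsor route is open to interpretation and the safety record is intact, so the loss is prompt independent oversight, not data.

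The exposure is at most 180 laser sessions. Few reports are likely to be affected, since section 7.1.1 anticipates that severe events will be rare, but no rate is given. The conclusion assumes that the gloss in 7.2.2 is read as a definition and that the cited REC procedure does not override it. It needs correction despite the small expected number, because the rule omits the harm for which such reporting matters most in this trial.

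**What to change.** - In section 7.2.2, define related to the study so that it covers events resulting from the randomised laser sessions as well as from biopsies and blood sampling.
- Apply the same definition to the 24-hour sponsor report in section 7.2.1.
- Reconcile the observational-cohort and standard-care wording in sections 3.1, 6.2.1, 6.2.2 and 7.2.2 with the randomised comparison in sections 5.4 and 8.2.
- State which events in section 7.1.1 count as expected for reporting, and in particular whether the rare severe ones do. Without this, an event newly counted as related could still be argued out of the REC report as expected.
- Check the new wording against the cited REC procedure.

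The cost is a short protocol amendment and possibly a few more serious adverse event reports. No new data collection is needed, because causality and expectedness are already recorded for every event.
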